#### End of session checklist

A session checklist [20] will be used to identify the extent to which specific program content and methods were covered as intended in each session.

### Data collection

#### Assessment procedures T1-T5

Data will be collected at three sites (Brisbane, Gold Coast, and Townsville) and five main time points (T1 to T5). The Time 1 (T1) assessment (pre-test) will be conducted one week prior to program delivery. Time 2 (T2) assessment (post-test) will occur one week after program completion for the intervention group and 5 weeks after Time 1 for the waitlist control group. Time 3 (T3), Time 4 (T4) and Time 5 (T5) assessments will be conducted 6 months, 12 months and 18 months after program completion respectively.

#### Program and process evaluation

Two trained facilitators employed by the not-for-profit agency, Act for Kids, will deliver all program sessions. Facilitators have qualifications in early childhood education, psychology, or child protection. First grade teachers will be present during the sessions. At the start of each session an attendance record will be taken and a brief review of the previous session content covered. At the end of each session facilitators will record the concepts covered and any factors impacting that session’s program delivery. In 10 % of sessions a research assistant will attend to audit the session content.

### Planned analyses

Mixed factorial analyses of variance (ANOVAs) will be used to examine the effectiveness of the program for primary outcomes. Analyses will be conducted to assess differences between the intervention and waitlist control conditions over time using 2 (Group: intervention, waitlist-control) x 3 (Time: T1, T2, T3) mixed ANOVAs. Primary or target outcomes include children’s knowledge of program concepts, intentions to use program knowledge, skills, and help-seeking strategies, and anxiety as a result of program participation. T-tests will be conducted to examine the difference between groups in use of program skills and disclosure during the simulated situation conducted at T2 and T3.

Following the 6-month follow-up of the children who received the program, data will be analysed to assess stability of improvement in the treatment group from post to, 6-, 12- and 18-month follow-up. One-way ANOVAs will also be conducted for these variables for the intervention group across the five time points (T1, T2, T3 and T4, T5).

Hierarchical linear modelling [37] will be used to examine any effects of the hierarchical structure of the study design. If there are hierarchical effects, this analysis will be used to account for influences of classroom (level 2) and school level effects (level 3), while examining the effects of condition (Emmy/waitlist) and within student changes over time. Regression will be used to test the mediation analyses and to examine any effects of moderators (e.g. demographic variables, parental stress, dose–response) to determine which factors may differentiate intervention effects. Intent-to-treat analyses will also be conducted to account for potential effects of differential drop-out.

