**Methods/Design:**

A three-site cluster randomised controlled trial (RCT) of Learn to be safe with Emmy and friends™ will be conducted with children in approximately 72 first grade classrooms in 24 Queensland primary (elementary) schools from three state regions, over a period of 2 years. Entire schools will be randomised, using a computer generated list of random numbers, to intervention and wait-list control conditions, to prevent contamination effects across students and classes. Data will be collected at baseline (pre-assessment), immediately after the intervention (post-assessment), and at 6-, 12-, and 18-months (follow-up assessments). Outcome assessors will be blinded to group membership. Primary outcomes assessed are children’s knowledge of program concepts; intentions to use program knowledge, skills, and help-seeking strategies; actual use of program material in a simulated situation; and anxiety arising from program participation. Secondary outcomes include a parent discussion monitor, parent observations of their children’s use of program materials, satisfaction with the program, and parental stress. A process evaluation will be conducted concurrently to assess program performance.

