### Aims

The aim of this study is to conduct an empirical assessment, using a cluster randomised-controlled trial [21], of key outcomes of the *Learn to be safe with Emmy and friends*™ program. Specifically, the current study will test the following five hypotheses:When compared to children in the waitlist condition for the same period, children in the intervention condition will show the following changes from pre-test to post-test:significantly greater increase in knowledge of interpersonal safetysignificantly greater ability to distinguish between safe and unsafe situationssignificantly greater intention to engage in safe responses to unsafe situationssignificantly greater confidence to take appropriate action in unsafe situations
When compared to parents/guardians of children in the waitlist condition for the same period, parents/guardians of children in the intervention condition will report significantly greater increases in their child’s knowledge of interpersonal safety and use of self-protective skills.Post-intervention, children in the intervention condition will:refuse a simulated in vivo lure by an unfamiliar adult at post-intervention at a higher rate than children in the waitlist condition.disclose the presence of an unfamiliar adult i) earlier; and ii) at a higher rate, than children in the waitlist condition.
Children’s post-intervention knowledge of interpersonal safety will be positively correlated with both behavioural intentions, application of self-protective skills, and disclosure.Children’s anxiety scores will not change from pre-intervention to post-intervention.

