## Methods/Design

The Human Research Ethics Committees at Griffith University (GU Ref No: PSY/48/14/HREC) approved this study, as did the Research Committee at the Department of Education and Training, Queensland. It is also registered with the Australian and New Zealand Clinical Trials Register (ACTRN12615000917538) and has received Australian Research Council funding under the Linkage Projects scheme (ID: LP130100304) in a partnership between Griffith University, James Cook University, Queensland University of Technology and the not-for-profit organisation, Act for Kids.

The study consists of a three-site cluster randomised control trial using a waitlist-control group. The unit of randomisation will be the school. The unit of analysis will be individual children; however the nesting effects of classes, schools, and site location will be taken into account through hierarchical modelling. Data from parents/guardians about immediate child outcomes will be paired with the respective child data. The main outcome evaluation will be supplemented by a process evaluation using fidelity data from facilitators, session auditors, and satisfaction surveys completed by parents/guardians and teachers.

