#### Observed Protective Behaviours Test (OPBT)

This will be administered to children in the control and intervention conditions at either post-test evaluation or the six-month evaluation. A structured two-part in vivo behavioural situation has been developed by the first author expressly for this study and will be used to test children’s ability to implement the safety skills learned during *Learn to be safe with Emmy and friends*™. Part 1 will measure recognition of unsafe situations and theapplication of relevant safety skills. Children will be presented with a simulated unsafe situation enacted by an unfamiliar confederate. In the script for the unsafe situation after greeting the child, the interviewer will leave the room under the pretext of making a telephone call [30]. During the interviewer’s absence,a confederate will enter the room and ask the child to leave with them. The confederate will then remember that they have forgotten a bag and leave, asking the child to keep their presence a secret and dropping a pen to the floor as they leave. The manipulation will take approximately 1 min with the interviewer returning within 30 s of the confederate exiting and resuming the interview.

Part 2 will test children’s disclosure of the unsafe situation. In this, children will be presented with 6 prompts to disclose the presence of the confederate (e.g., “You probably didn’t notice if the pen was in the room before, did you?”). At the end of the interview, prior to administering the anxiety measure the confederate will return and the secret will be revealed. This will provide an opportunity for the interviewer to model disclosure of the unsafe situation with the child and engage in debriefing. The OPBTis based on behavioural skills training and measures used by Johnson et al. [31, 32] and Gunby et al. [33] in evaluations of children’s personal safety skills, as well as the secret-keeping scenario and seven point secret-keeping scale created by Dunkerley and Dalenberg [30].

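### The simulated-situation outcome is compared by child-level t-tests although schools are randomised, and the plan's hierarchical model is conditional and does not clearly cover it

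*Protocol article*

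**What the plan says.** All references are to the protocol article.

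- **Randomisation** (Methods/Design): "The unit of randomisation will be the school".
- **Clustering, general statement** (Methods/Design): "the nesting effects of classes, schools, and site location will be taken into account through hierarchical modelling". No condition is attached.
- **Clustering, analysis text** (Planned analyses): hierarchical linear modelling first looks for effects of the design's structure. Only if there are any does it account for classroom and school, while examining condition and change within students over time.
- **The named test** (Planned analyses): "T-tests will be conducted to examine the difference between groups in use of program skills and disclosure during the simulated situation", at T2 and T3.
- **When children are tested** (Observed Protective Behaviours Test): "at either post-test evaluation or the six-month evaluation". The division between the two times is not given.
- **The hypothesis** (Aims): intervention children will refuse "a simulated in vivo lure by an unfamiliar adult at post-intervention at a higher rate" than waitlist children. They will also disclose earlier and at a higher rate.
- **The scale** (Observed Protective Behaviours Test): scoring of the first part is not given. Disclosure is sought over six prompts, and the test draws on a seven-point secret-keeping scale.
- **Status of the outcome**: the abstract's primary outcomes include "actual use of program material in a simulated situation; and anxiety arising from program participation". The list in Planned analyses opens "Primary or target outcomes include children’s knowledge of program concepts", continues with intentions and anxiety, and omits the simulated situation.

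**The concern.** Children in one school share teachers, neighbourhood and programme delivery, so their responses are correlated. A t-test that counts each child as independent gives too small a standard error for a comparison of randomised schools, and rejects a true null hypothesis too often.

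The plan knows this: it inflates its sample size by a design effect. The test it names for this outcome then leaves the design effect out. This is the trial's only directly observed measure of behaviour and is primary in the abstract. A false-positive result here would be read as evidence that the programme changes what children do.

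The hierarchical model is not a secure remedy. It is conditional in one section and unconditional in another. As described, it models change within students, and a child tested once has none.

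**Working it through.** **Inputs from the plan.** Design effect about 1.5, 20% attrition and 60 children per school (Recruitment and participants); 24 schools (abstract), taken as 12 per arm. The plan states no significance level, intraclass correlation (ICC) or error rate for these t-tests, so there is no figure of its own to reproduce.

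**Assumptions.** Two-sided nominal 5%; equal school sizes; where stated, half of each school's children tested at each time; ICCs other than the implied one.

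**Formulas.** Design effect DE = 1 + (m − 1) × ICC, with m children tested per school. True type I error of the unclustered test = 2 × [1 − Φ(1.96/√DE)].

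**1. At the plan's design effect.** 1.96/√1.5 = 1.600, so the error is 0.110. With m = 60 the implied ICC is 0.5/59 = 0.0085.

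**2. Half tested at each time.** Same ICC, m = 30: DE = 1 + 29 × 0.0085 = 1.25; 1.96/√1.25 = 1.753; error 0.079.

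**3. If the 1.5 already contains attrition**, as its sentence can be read: 1.5 × 0.8 = 1.2; 1.96/√1.2 = 1.789; error 0.074.

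**4. Other ICCs (assumed).**

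| ICC | Error, m = 60 | Error, m = 30 |
|---|---|---|
| 0.01 | 0.12 | 0.08 |
| 0.02 | 0.18 | 0.12 |
| 0.05 | 0.32 | 0.21 |

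**5. Simulation.** Yes/no data, 12 schools per arm, 20,000 runs per setting. At ICC 0.0085 and m = 60 the child-level t-test rejects in 0.106 to 0.109 of null trials, in line with step 1. A t-test on school proportions rejects in 0.047 to 0.051 across all settings tried.

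**6. Does yes/no coding matter?** With ICC 0, the t-test on 0/1 data rejects in 0.047 to 0.052, the same as a test of proportions. The excess error comes from clustering, not from the coding.

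**7. Would the conditional rule rescue it?** Suppose it is applied to this outcome, with a 5% F-test for school variance within arms (22 degrees of freedom between schools). Its power is the probability that F exceeds its critical value divided by 1 + m × ICC/(1 − ICC). At ICC 0.0085 this is about 43% with m = 60 and 21% with m = 30, so clustering of the size the plan expects would usually be missed. Simulating the whole rule (normal outcome; school-level test if F is significant, otherwise the t-test) gives an error of about 7% for either m.

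**The case against.** The strongest reply is that clustering is not forgotten. Methods/Design says for the whole study that nesting will be handled, and Planned analyses has a hierarchical model. A reader might infer that the plan ignores school randomisation altogether; these statements do not support that. What stands is that the two sections conflict, and that the conditional model is not clearly meant for this outcome. The conflict also touches the ANOVAs.

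The size is open to dispute too. The 11% needs about 60 tested children per school, and testing each child at only one of two times lowers it. That stands, and is why a range is given.

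Three stronger readings are tempting but not supported:

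- **That a t-test is invalid because refusal is yes/no.** Yes/no scoring is inferred from the word rate in Aims, disclosure is graded, and step 6 shows almost no effect on the error rate. A logistic model is preferable because it estimates what the hypothesis states.
- **That each comparison falls short of the required 1350 children.** That figure is a whole-trial total with allowance for attrition and subgroup analyses. It is not a requirement at each time point.
- **That T2 and T3 should be pooled as the main test, with children randomised to test time within class.** Testing each child once is a legitimate design choice. The hypothesis concerns post-intervention behaviour, and the Discussion separates short-term change from retention, so pooling asks a different question. Mixing test times within a class could also let debriefed children tell classmates who are still to be tested.

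Finally, Planned analyses does not list the outcome as primary. That lessens the consequence if its list governs, but the abstract says otherwise and the two must agree.

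**Conclusion.** The point holds as one about clustering. Followed as written, the t-tests for the simulated situation do not respect randomisation by school. At an assumed nominal 5% level their true type I error is about 11% at the plan's design effect with about 60 children per school. It is about 8% with an assumed even split between T2 and T3, and about 7% if the design effect already includes attrition. At an assumed ICC of 0.05 it reaches 21% (30 per school) to 32% (60 per school). Making adjustment depend on detecting clustering in about 24 schools reduces the excess but does not remove it. The sections on clustering conflict, and so do the two primary outcome lists. The choice between a binary and a continuous model is minor.

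**What to change.** 1. In Planned analyses, replace the t-tests by models that always include random effects for school and class, with region as a fixed effect and a small-sample correction for about 24 schools. Use mixed logistic regression for refusal and for any disclosure, and a mixed ordinal or linear model for the prompt at which disclosure occurs. An equivalent school-level analysis would also serve.
2. Delete the condition that hierarchical effects must first be found, so that Planned analyses agrees with Methods/Design. State that the clustered analysis applies to outcomes measured once per child.
3. Make the primary outcome lists in the abstract and Planned analyses agree on the simulated situation.

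**Cost.** Analysis wording only: no new data, visits or change to when children are tested. Honest standard errors will be larger than the t-test's, by a factor of √1.5 = 1.22 at the plan's design effect. That is precision the t-test never had.

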#### Application of Protective Behaviours Test-Revised (APBT-R)

The APBT-R will be administered both at pre- and post-test evaluation. This is a revised version of the original APBT developed by Dale et al. [20] as a six-item, child-report measure assessing children’s intention to apply self-protective knowledge and skills, and seek appropriate help in unsafe situations. In the APBT-R, unsafe scenarios were retained and two new safe scenarios were added. Two developmental psychologists and two child abuse prevention experts screened new safe scenarios. The APBT-R thus includes two safe and four unsafe scenarios presented to children by interviewers as verbal narratives accompanied by simple line drawings. Children’s responses for unsafe scenarios will be rated according to the degree to which they are self-protective. Scores for each scenario will be summed across unsafe scenarios to provide a Total Self-Protective Intention score with higher scores indicating greater protective behaviour intentions. Children will also be asked to rate for all scenarios whether or not each scenario is safe on a yes/no response. These responses will be marked as correct or incorrect and summed to further provide a Total Risk Accuracy score with higher scores indicating greater accuracy in classifying scenarios.

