#### Demographics

Family and child demographic information will be collected in 10 items including child gender, child age, parental gender, parental age, family structure, parental income and parental education. In these items family community engagement and the child’s social and school engagement will also be assessed.

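### The t-tests planned for the simulated situation (OPBT) use none of the pre-intervention information the trial collects, at a modest cost in precision and none in bias

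*Protocol article*

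**What the plan says.** Under Planned analyses, the other child outcomes (knowledge, intentions, anxiety) are analysed by "2 (Group: intervention, waitlist-control) x 3 (Time: T1, T2, T3) mixed ANOVAs", which include the pre-test. The simulated situation is treated differently: "T-tests will be conducted to examine the difference between groups in use of program skills and disclosure during the simulated situation", at T2 and T3. No covariate is named.

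The OPBT section places the test "at either post-test evaluation or the six-month evaluation", so no child has a pre-intervention OPBT score.

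Pre-intervention information does exist:
- Assessment procedures T1-T5: "The Time 1 (T1) assessment (pre-test) will be conducted one week prior to program delivery".
- APBT-R section: "The APBT-R will be administered both at pre- and post-test evaluation".
- Knowledge (ProBeQ) is analysed from T1, so a T1 score exists.
- Demographics, reported by parents: "child gender, child age, parental gender, parental age, family structure".

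Elsewhere under Planned analyses, demographic variables appear only as possible moderators. The hierarchical model applies only if hierarchical effects are found. It names classroom, school, condition and time, and no baseline covariate.

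The status of the OPBT varies. The Abstract lists it among the primary outcomes; the list of primary or target outcomes under Planned analyses leaves it out.

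**The concern.** For the other child outcomes, the pre-test score carries much of what can be known about a child beforehand. The OPBT has no such score, so any gain in precision must come from other variables measured before the programme. The named test cannot use them.

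The OPBT is the trial's only directly observed behaviour. It may also be divided over two visits, in which case each comparison rests on part of the sample. The number of randomised schools is small, so recoverable precision is worth having. What is at stake is a somewhat wider confidence interval and somewhat lower power than the same data could give.

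**Working it through.** **The plan's own figures.** No power or sample size is stated for the OPBT. The overall planned size reproduces: 60 × 9 × 3 = 1620. The required 1350 does not follow from the stated steps: 100 × 2 × 3 = 600 and 600 × 1.5 = 900; reaching 1350 takes a second, unstated factor of 1.5. Nothing below depends on this.

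**Inputs.**
- Schools: 24 (Abstract; eight in each of three regions under Recruitment and participants), taken as 12 per arm. The sample-size paragraph uses nine per region, which would be 27.
- Tested children per school at one visit: 60 × 0.8 × 0.5 = 24. The 60 and the 20% attrition are in the article; testing half at each visit is an assumption.
- Assumed: two-sided alpha 0.05, 80% reference power, school ICC 0.01 to 0.10, and the shares of OPBT variance explained by the covariates between schools (R²b) and within schools (R²w).

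**Formula.** With the outcome SD set to 1,

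Var(difference) = (2/12) × [ICC(1 − R²b) + (1 − ICC)(1 − R²w)/24].

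The effect is set so that the unadjusted school-level analysis has 80% power on 22 df, which requires 2.93 standard errors. Power is then recomputed from the noncentral t distribution with the smaller standard error on 21 df. A stricter version charges one df for each of the four covariates (18 df).

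**Same R² between and within schools.** The SE ratio is √(1 − R²), whatever the ICC.

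| R² | SE ratio | Power, 21 df | Power, 18 df |
|---|---|---|---|
| 2% | 0.990 | 80.6% | 80.0% |
| 4% | 0.980 | 81.4% | 80.8% |
| 9% | 0.954 | 83.4% | 82.8% |
| 16% | 0.917 | 86.2% | 85.6% |

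**9% explained within schools, none between (21 df).**
- ICC 0.01: bracket 0.01 + 0.99/24 = 0.05125 falls to 0.01 + 0.99 × 0.91/24 = 0.04754. SE falls 3.7%; power 82.7%.
- ICC 0.05: 0.08958 falls to 0.08602. SE falls 2.0%; power 81.4%.
- ICC 0.10: 0.13750 falls to 0.13413. SE falls 1.2%; power 80.8%.

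**Unfavourable case.** With 4% within, none between and ICC 0.10, the bracket goes from 0.1375 to 0.1360. The SE falls about 0.5%. Power is just over 80% on 21 df and 79.6% on 18 df. Weaker covariates still would give slightly less.

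**Favourable case.** With 9% within and 30% between, power is 85.0% at ICC 0.01 and 89.5% at ICC 0.10. Nothing in the article supports so large a share between schools.

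**Why the school term must come first.** These figures compare two analyses that both respect school randomisation. The t-test as written makes no allowance for schools. With design effect 1 + (m − 1) × ICC, its true type I error is 2[1 − Φ(1.96/√DE)]. For m = 24 and ICC 0.01, DE = 1.23 and the error is 0.077; for m = 48 (60 × 0.8, all tested at one visit) and ICC 0.05, DE = 3.35 and the error is 0.284. Covariates do not cure that.

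**The case against.** The strongest reply is that nothing here is an error. An unadjusted comparison of randomised schools is unbiased, and chance differences in age or prior knowledge are sampling error that a correct standard error already covers. A list of covariates is also something a condensed article may leave to an analysis plan. The first part stands, and it confines the point to precision. The second carries less weight, because the article does not leave the method open: it names a test that admits no covariates.

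Several stronger readings are tempting, and the documents do not support them:
- A reader might infer that Hypothesis 4 shows the T1 scores to be prognostic. It expects that "knowledge of interpersonal safety will be positively correlated with both behavioural intentions, application of self-protective skills, and disclosure", but it concerns knowledge after the intervention. It makes a link with T1 knowledge plausible and gives no size.
- A reader might infer that the authors considered adjustment and rejected it. The article does not discuss it.
- A reader might take all four covariates as recorded for every child at T1. Age and sex come from a parent form whose timing is not stated, and some values will be missing.
- A reader might call the adjustment free. It adds four parameters and a missing-value rule, and with weak covariates and few schools it can cost a fraction of a percentage point of power.
- A reader might treat the OPBT as unambiguously primary. The Abstract and Planned analyses differ on this.

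It is also fair to say that the lack of a school term is the more serious weakness of the same sentence. The covariates are worthwhile only as an addition to that repair.

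**Conclusion.** The point holds as a modest improvement in efficiency. The OPBT comparison has no baseline score, the named test uses no pre-intervention information, and suitable variables are already being collected. The comparison is not biased by leaving them out.

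The likely gain runs from nothing useful, if the covariates explain about 2% of the variance, to about six percentage points of power at 16%. It is one to three points if 9% is explained within schools only. The worst case examined is a loss of 0.4 points. Every R² and ICC is assumed, as are 12 schools per arm and 24 tested children per school. For yes/no refusal and disclosure the linear R² figures are approximate.

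**What to change.** Replace the OPBT t-tests by a regression that contains the school term required by randomisation of schools, with four pre-specified child-level covariates: T1 ProBeQ total, T1 Total Self-Protective Intention, child age and child sex. Do not use post-intervention knowledge as a covariate, since the programme is meant to change it.

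For yes/no refusal and disclosure, report the covariate-standardised risk difference, with uncertainty that allows for schools. Fill missing covariate values with the overall mean across both arms, so that no tested child is lost.

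The change takes a sentence or two under Planned analyses and needs no new data. The cost is four more parameters, the missing-value rule, and the negligible loss of power if the covariates prove weakly prognostic. Naming the covariates now also prevents their being chosen after the results are seen.

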### Recruitment and participants

The study will be conducted in first grade classrooms with children aged 5–6 years in three education regions in Queensland, Australia: Brisbane (Metropolitan Region, urban schools), Gold Coast (South East Region, urban schools), and Townsville (North Queensland Region, rural schools). Eightschools in each region will be randomly selected to participate. Trained research assistants not involved in data collection will initially contact schools. An information sheet detailing the *Learn to be safe with Emmy and friends*™ program and explaining the evaluation will be sent to school principals who will be asked to provide consent for their school’s participation. Randomisation will be conducted following principal consent, after which time, schools will be asked to distribute standardised information sheets with consent forms (either waitlist-control or intervention version) to parents/guardians (hereafter, parents) of all children enrolled in first grade. Parents return consent forms to the school if they agree for their child to participate.

A simple random sampling strategy with individuals as the primary sampling unit was assumed, and G*Power was then used to estimate sample size. This returned a suggested total sample size of at least 100 children per group at each of three sites. Based on similar studies [22] that have used cluster sampling with schools as the primary sampling unit, the sample size with this design effect was estimated to be approximately 1.5, taking into account potential attrition of (20 %) owing to student absences and/or mobility. In addition, enough power will be needed to examine the effects for subgroups (sex/school/family/stress, etc.). Therefore, a total sample size of at least 1350 is required in this study to test the effectiveness of the intervention. Assuming conservative class sizes of 20 students per class (60 children per school; 9 schools in each region), a final initial sample size of 1620 Year 1 children and their parents is planned to give sufficient power for this study.

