### Randomisation

After school recruitment and principal consent, a concealed randomisation process will be undertaken using a computer-generated list of random numbers. Entire schools will be randomised to intervention or control to prevent knowledge and skill sharing among students across conditions. Researchers conducting data collection and data analysis will be blinded to group membership.

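### The article promises that site location will be taken into account, but none of the models it specifies contains a site term; region should enter each between-arm model as a fixed effect

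*Protocol article*

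**What the plan says.** The opening of Methods/Design states that "the nesting effects of classes, schools, and site location will be taken into account through hierarchical modelling".

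Planned analyses then sets out the models:

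- The other primary outcomes are compared by "2 (Group: intervention, waitlist-control) x 3 (Time: T1, T2, T3) mixed ANOVAs". Group and time are the only factors.
- For the in vivo test, "T-tests will be conducted to examine the difference between groups in use of program skills and disclosure during the simulated situation".
- The hierarchical model is conditional: "If there are hierarchical effects, this analysis will be used". On its levels, the section says "this analysis will be used to account for influences of classroom (level 2) and school level effects (level 3"). Site is neither a level nor a covariate, and it is not among the examples of moderators.

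Site is nonetheless part of the design. Recruitment and participants draws a fixed number of schools from each of three regions, "Brisbane (Metropolitan Region, urban schools), Gold Coast (South East Region, urban schools), and Townsville (North Queensland Region, rural schools"), and builds the sample size up per group at each site. Under Randomisation, "a concealed randomisation process will be undertaken using a computer-generated list of random numbers", with no mention of stratification by region.

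**The concern.** An analyst cannot follow both sections: one promises that site is handled, and the other fixes models that do not handle it. Schools, not children, are randomised, so the precision of the group effect depends mainly on variation between 24 schools. In a three-level model without region, any urban/rural or regional difference in outcome sits in the school-level variance, which is the error for the group effect. A chance surplus of one region's schools in one arm would also go uncorrected.

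The effect is fullest for the simulated situation, which is given only at post-test or six months and has no T1 value. Where there is a T1 value, a constant regional difference cancels in the group-by-time contrast, and only regional differences in change remain.

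The promise also needs rewording. It lists site among the nesting effects, but a variance component estimated from three regions would be of little use.

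**Working it through.** The article gives no figure for regional variance, so there is nothing of its own to reproduce. The contradiction is textual; the arithmetic below only sizes its consequence.

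**Inputs**

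- Schools: 24, 8 per region (Abstract; Recruitment and participants). The sample-size text uses 9 per region, a separate discrepancy.
- Children analysed per school: m = 60 × (1 − 0.20) = 48.
- Assumed: school ICC of .02 or .05, where the ICC is the total between-school variance with total variance 1; share s of that variance lying between regions; one time point with no baseline; 80% power without a site term.

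**Model that respects school clustering, arms balanced within region**

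Variance of a school mean without region: v = ICC + (1 − ICC)/m. With region fixed: v2 = ICC(1 − s) + (1 − ICC)/m.

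The non-centrality that gives 80% power on 22 df (24 − 2) is about 2.93. It is rescaled by √(v/v2) and evaluated on 20 df.

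| ICC | s | v | v2 | Variance reduction | Power |
|---|---|---|---|---|---|
| .02 | 10% | .0404 | .0384 | 5% | 81.6% |
| .02 | 20% | .0404 | .0364 | 10% | 83.6% |
| .02 | 30% | .0404 | .0344 | 15% | 85.6% |
| .05 | 10% | .0698 | .0648 | 7% | 82.5% |
| .05 | 20% | .0698 | .0598 | 14% | 85.4% |
| .05 | 30% | .0698 | .0548 | 21% | 88.2% |

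With s = 0, power is 79.6%: the price of the 2 df.

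**If allocation is a 12/12 split not balanced by region**

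With a intervention schools among the 8 in a region, the adjusted variance is proportional to 1/Σ[a(8 − a)/8], the sum running over the three regions. Exact balance gives a sum of 3 × (4 × 4/8) = 6. All three regions split 4:4 with probability 70³/2,704,156 = 13%. Averaged over all splits, adjustment inflates the variance by a factor of about 1.11.

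- ICC .05, s = 20%: 0.857 × 1.107 = 0.95, so the 14% reduction becomes about 5%.
- ICC .05, s = 10%: 0.928 × 1.107 = 1.03, a small loss.

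**The t-tests as written**

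These take children as independent. Their standard error relative to the true one is about √[(1/48)/v]:

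- ICC .02: √(.0208/.0404) = 0.72
- ICC .05: √(.0208/.0698) = 0.55

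Taking region out of the child-level residual would multiply the residual SD by √(1 − ICC × s). That is a change of 0.2% at ICC .02 with s = 20%, and of 1.3% at ICC .05 with s = 50%.

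**The case against.** The strongest reply has four parts.

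- **The t-tests.** A reader might infer that the missing site term makes the intervals for the simulated situation too wide. The planned t-tests do not support that. They ignore school, so their standard errors are about 55–72% of the true ones and their intervals are too narrow; the site term would barely change their width. This stands, and the precision argument applies only once school is modelled.
- **The size.** The power figures assume arms balanced within region. A sample size set per group and site implies this, but Randomisation does not state it. They also assume 48 children per school. If each school's children are divided between the two occasions for the simulated test, about 24 remain at each; at a 20% share, power is then 82% rather than 84% (ICC .02) or 84% rather than 85% (ICC .05). Larger regional shares would give larger gains, but nothing in the article supports a particular share. This also stands: the tabulated gains are at the upper end.
- **Validity.** Omitting site is not shown to bias the comparison or inflate its type I error in a model that includes school. That is right, and the point should not be read as a validity failure.
- **Condensed reporting.** An article may leave fixed covariates to a fuller plan, and naming random levels does not exclude a site covariate. This weighs less. The article makes an explicit promise about site and then spells out each model without it, so the mismatch is in the text itself.

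**Conclusion.** The contradiction holds: site is promised in Methods/Design and absent from every model in Planned analyses. It should be corrected, although on its own it invalidates no primary conclusion.

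In a model with school effects, fixed region terms would raise 80% power to about 82–88%. This rests on ICCs of .02 to .05, 10–30% of between-school variance lying between regions, 48 children per school, no baseline value and arms balanced within region. The gain shrinks, or turns into a small loss, without regional balance or where regions barely differ, and it is smaller for outcomes measured at T1.

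The absence of stratification from the Randomisation text does not show that allocation is unstratified, only that balance by region cannot be taken for granted. For the simulated-situation t-tests, the larger defect is the missing school and class terms.

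**What to change.** - In Planned analyses, specify for every between-arm model, including those for refusal and disclosure in the simulated situation, random effects for class and school and two fixed indicator terms for region (Brisbane, Gold Coast, Townsville). This should not depend on whether hierarchical effects are detected.
- In Methods/Design, reword the commitment so that class and school are nesting levels and site is a fixed effect.

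The cost is wording plus 2 of the 22 school-level degrees of freedom. Region is known for every school, so no new data are needed. If regions do not differ, power slips from 80% to 79.6% with arms balanced within region; with chance imbalance, the average variance inflation of about 11% shown above applies. The change is best made before outcome data are seen, so that a site term does not look post hoc.
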